### Randomization and treatment

Eligible participants with appropriately signed informed consent will be randomized to either the ipragliflozin group or control group (ratio 1:1) using the web-based minimization method with biased coin assignment balancing [27, 28] for age (<65, ≥65 year), HbA1c level (<7.0, ≥7.0 %), systolic BP (<135, ≥135 mmHg), use of statins, and use of biguanides at the time of screening.

All participants will be followed-up for 24 months. Although a specific numerical goal in glycemic control such as HbA1c level is not set for the study, all participants need to be treated to achieve a personalized goal recommended by the treatment guideline in Japan (details in Additional file 1) [26]. Participants who are assigned to the ipragliflozin group receive ipragliflozin 50 mg once daily in addition to their background medical therapy. In accordance with official recommendation regarding use of SGLT2 inhibitor from the Japan Diabetes Society [29], patients aged ≥75 years should be most carefully followed up with particular attention to development of volume depletion-related adverse drug reactions [30]. If the personalized goal is not achieved, the dose of ipragliflozin can be increased by the investigators to 100 mg once daily. Participants who are assigned to the control group continue their background therapy. Within the appropriate range of the therapeutic goal, the participant’s background therapy will be, in principle and if possible, unchanged during the study in both groups. However, if participants cannot achieve their glycemic goal, co-administration of anti-diabetic agents other than SGLT2 inhibitors or increased dosages of the other anti-diabetic agents in both groups may be considered by investigators, with caution being taken to prevent the development of hypoglycemia. However, because pioglitazone is known to have a suppressive effect on the progression of IMT, compared to glimepiride [22], it is prohibited to prescribe it or change its dose during the study. After the study is completed, all participants can continue any anti-diabetic treatment in accordance with their individual condition.

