### Statistical considerations

#### Sample size estimation

Due to the lack of data on the effect of SGLT2 inhibitors on carotid IMT, we referred to the statistical data from the CHICAGO study [22] and PROLOGUE study [25]. In the CHICAGO study, pioglitazone caused a significant inhibition of the progression of CCA-IMT (−0.0010 mm after 72 weeks), compared to glimepiride (+0.0120 mm after 72 weeks). We estimated the changes from baseline would be −0.0013 mm (pioglitazone) and +0.016 mm (glimepiride) after 96 weeks. Based on the assumption that ipragliflozin may inhibit the progression of CCA-IMT to the same extent as pioglitazone, we estimated the group difference as 0.016 (ipragliflozin −0.001 and control +0.015) ±0.06 (standard deviation). At a significant level of 5 % (two-sided), the sample size of 222 patients per arm provides a power of 80 % for each comparison. Allowing for a dropout rate of 5 %, 240 patients in each arm (a total of 480 patients) provides sufficient statistical power for the study.

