#### Statistical analysis plan

The analyses of the primary and secondary endpoints will be performed in the full analysis set (FAS), which includes all participants who received at least one dose of treatment during the study period and did not have any serious violation of the study protocol such as not providing informed consent, registration outside of the study period, or data collected after commencement of treatment.

Summary statistics will be calculated for the baseline characteristics including the frequencies and proportions for categorical variables and means ± standard deviations for continuous variables. The patient characteristics will be compared using Chi square tests for categorical variables, t tests for normally distributed continuous variables, or the Wilcoxon rank sum tests for continuous variables with a skewed distribution.

The analysis plan is similar to that used in previous studies we have conducted [25, 31, 32]. In brief, for the primary analysis comparing treatment effects, the baseline-adjusted means and their 95 % confidence intervals, estimated by analysis of covariance of the change in average carotid IMT at 24 months, will be compared between the treatment groups (ipragliflozin group vs. control group). The results will be adjusted by allocation factors. The primary analysis will not include missing observations, with the mixed effects model for repeated measures (MMRM) being used as a sensitivity analysis to examine the effect of missing data. In addition, MMRM will be used as a sensitivity analysis to examine the outcomes at baseline and 24 months modelled as a function of time, treatment, and treatment-by-time interaction. The secondary analysis will be performed in the same manner as the primary analysis.

All comparisons are planned and all *P* values will be two sided. *P* values <0.05 will be considered statistically significant. All statistical analyses will be performed using SAS software version 9.4 (SAS Institute, Cary, NC, USA). The statistical analysis plan will be developed by the principal investigator and a biostatistician before completion of patient recruitment and database lock.

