This study has several limitations. First, the PROTECT study is not a double blind placebo-controlled trial, but rather an open label design. Unexpected bias towards the assessment of outcomes resulting from the physicians’ choice of treatment may occur. To avoid this possible bias, there are strict requirements that the participants’ background treatment will, in principle and if possible, remain unchanged during the study. In addition, carotid IMT, a key endpoint in the study, will be measured at a central laboratory, and all the data will be managed and statistically analyzed in a blinded fashion. Second, because the duration of the study is 24 months, it is possible the additional anti-diabetic agents administered when glycemic control becomes worse, especially in the control group, may influence outcomes. It is therefore important to take into account that pioglitazone and some other DPP-4 inhibitors may also prevent progression of carotid IMT in patients with T2DM [22–24]. Third, because the investigators who are participating in the PROTECT study are mainly cardiologists, there may be potential variety of treatment or judgement in the management of diabetes. Therefore, the Steering Committee recommends clinical practice will be performed according to the participants’ comprehensive conditions based on the treatment guideline in Japan [26]. Last, patient’s renal function, estimated glomerular filtration rate (eGFR), is not included as an allocation factor, although patients with severe renal dysfunction (eGFR < 45 ml/min/1.73 m^2^) or receiving dialysis are excluded. The patient’s kidney function is one of major determinants of urinary glucose excretion by SGLT2 inhibitor treatment. Previous studies reported that urinary glucose excretion in patients with lower levels of eGFR was actually decreased, and improvement of glycemic control was lower than patients without impairment of renal function [87, 88]. However, there were SGLT2 inhibitor-induced reductions in body weight and blood pressure independently of patient’s renal function [89]. Thus, we have speculated that anti-atherosclerotic effect may be, in part, caused by ipragliflozin independently of glycemic control and renal function at baseline.

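### On its natural reading, the primary ANCOVA enters age, HbA1c and systolic BP only as two-level groups; using the recorded baseline values would give a small, nearly free gain in precision

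*Protocol article*

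**What the plan says.** - **Protocol article, Statistical analysis plan.** The primary analysis is an ANCOVA of the change in carotid IMT at 24 months, giving baseline-adjusted means by arm. On further covariates it says: "The results will be adjusted by allocation factors". Secondary endpoints are to be handled in the same way. The account is presented as a summary, and a full analysis plan is to follow before recruitment is complete and the database is locked.
- **Protocol article, Randomization and treatment.** Minimization balances "for age (<65, ≥65 year), HbA1c level (<7.0, ≥7.0 %), systolic BP (<135, ≥135 mmHg), use of statins, and use of biguanides". This is the only definition of the allocation factors in the article.
- **Protocol article, Measurements.** Age is recorded before randomization; blood pressure and HbA1c are measured at baseline.
- **Protocol article, Sample size estimation.** The inputs are "we estimated the group difference as 0.016" mm and "0.06 (standard deviation".
- **Protocol article, Discussion (limitations).** The article notes that "estimated glomerular filtration rate (eGFR), is not included as an allocation factor".

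**The concern.** Minimization needs categories; an ANCOVA does not. Eligibility in Table 1 runs from age 20 with no upper limit and from HbA1c 6.0% to below 10.0%. The under-65 group can therefore span up to 45 years of age, and the upper HbA1c group spans three percentage points. A two-level covariate treats everyone within such a group as alike. Any association between the actual value and IMT change within the group then stays in the error term.

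What is at stake is precision only: a slightly wider confidence interval than the collected data allow, for the primary endpoint and for the secondary endpoints analysed in the same way.

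**Working it through.** **Step 1. Reproduce the planned sample size.** Inputs from Sample size estimation: difference 0.016 mm, SD 0.06 mm, "At a significant level of 5 % (two-sided"), power 80%.

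n per arm = 2 × (0.06/0.016)² × (1.960 + 0.842)² = 220.7, so 221 by the normal approximation. The noncentral t calculation gives 222, matching "the sample size of 222 patients per arm provides a power of 80"%. Power at 222 per arm is 80.2% (normal) or 80.1% (t).

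No variance reduction for covariates enters this calculation. Any precision from covariates, in either coding, comes on top of the stated 80%.

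**Step 2. Number analysed.** The article states "Allowing for a dropout rate of 5 %, 240 patients in each arm". With 5% lost, 240 × 0.95 = 228 per arm. With SD 0.06 and no covariate credit, power at 228 is 81.3%.

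**Step 3. What a two-level cut keeps.** For a normally distributed covariate cut at quantile p, the share of its explained variance that survives is k = φ(z_p)² / [p(1 − p)].

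| Cut | k |
|---|---|
| 50/50 | 0.637 |
| 40/60 | 0.622 |
| 30/70 | 0.576 |
| 20/80 | 0.490 |

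The article does not say how participants will fall around 65 years, 7.0% or 135 mmHg. I take k from 0.64 (all median cuts) to 0.55 (a mix of less even cuts).

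**Step 4. Residual variance and power.** Let R² be the share of the variance left after baseline IMT that the three continuous values explain together. The article gives no figure, so 2%, 5% and 10% are assumptions. I also assume linear associations, and that 0.06 mm is the SD before these covariates are added.

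- Residual variance, two-level coding: 0.06² × (1 − kR²)
- Residual variance, continuous coding: 0.06² × (1 − R²)
- Ratio: (1 − R²)/(1 − kR²)

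Example with R² = 0.05 and k = 0.64: 0.95/0.968 = 0.981, a cut of 1.9%; 480 × 0.019 ≈ 9 participants.

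| Assumed R² | Cut in residual variance | Equivalent participants out of 480 | Power at 228 per arm, two-level | Power, continuous | Gain (points) |
|---|---|---|---|---|---|
| 2% | 0.7–0.9% | about 4 | 81.7% | 82.0% | about 0.3 |
| 5% | 1.9–2.3% | 9–11 | 82.3–82.5% | 83.2% | 0.7–0.9 |
| 10% | 3.8–4.8% | 18–23 | 83.4–83.7% | 85.1% | 1.4–1.7 |

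Power uses the normal approximation throughout. If all three cuts fell at 20/80 (k = 0.49), the R² = 10% row would reach 1 − 0.90/0.951 = 5.4% and about 2.0 points, so the conclusion is not sensitive to the cut.

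**The case against.** **The coding is not stated.** The article does not say in what form the allocation factors enter the model, and covariate coding commonly belongs in the analysis plan, which is not shown. This stands in part. Two-level adjustment is an inference from the only definition given. But the article does name the covariate set, so the point concerns a stated choice and is put as a recommendation, not as an omission.

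**Adjusting for the minimization factors is standard and valid.** This stands. Two-level adjustment biases nothing.

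**The gain is small and rests on assumed R².** This stands too. At the low end it is worth about 4 of 480 participants.

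**Continuous terms assume linearity.** True. Keeping the two-level groups alongside them allows a step at each cut, and a poorly fitting line would mainly forgo some of the gain.

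**Secondary endpoints benefit unevenly.** Fair. When the outcome is change in HbA1c or systolic BP, the recorded baseline value of that variable should already be in the model, so less is left to recover.

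A reader might infer two stronger points that the documents do not support:

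- *That coarse coding leaves the trial short of 80% power.* It does not, because the sample size takes no credit for covariates.
- *That eGFR is unbalanced and that adding it as a covariate would settle the limitation in the Discussion.* The Discussion says only that eGFR was not an allocation factor. It reports no imbalance, and randomization balances eGFR in expectation. It links kidney function to urinary glucose excretion under the drug, not to IMT change, and speculates that the anti-atherosclerotic effect may be partly independent of baseline renal function. That limitation concerns how strongly the drug works at different eGFR levels, which is effect modification; a main-effect covariate does not address it.

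**Conclusion.** The point holds as a minor efficiency improvement. It is not an error, a contradiction or a threat to validity. On the natural reading, the model discards within-group information on age, HbA1c and systolic BP that the trial already holds. Across the assumed R² of 2% to 10%, continuous coding would cut residual variance by about 0.7% to 4.8% and add about 0.3 to 1.7 power points at 228 per arm. These figures rest on the assumed R², on roughly normal covariates with linear associations, and on cuts that keep about 55% to 64% of the explained variance. If the three values predict IMT change hardly at all, the gain is close to zero.

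**What to change.** Specify in the analysis plan, before any 24-month data are seen, that the primary and secondary ANCOVA models contain:

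- treatment and the baseline value of the outcome;
- statin use and biguanide use (yes/no);
- age, HbA1c and systolic BP as continuous covariates (entered once where one of them is itself the baseline value of the outcome);
- the two-level allocation groups for those three as well, if wished.

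Continuous baseline eGFR is at most an optional prespecified covariate against chance imbalance, and should not be presented as resolving the limitation in the Discussion.

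The cost is one line of text and no new data on age, HbA1c or systolic BP. If the two-level groups are kept, it takes three extra degrees of freedom; if they are replaced, none. With 2 × 228 = 456 participants expected in the analysis, that is negligible. The other price is the linearity assumption.

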### Study outline and follow up

After informed consent has been obtained and the eligibility assessment is completed, all eligible participants will be randomized and assigned into either the ipragliflozin group or standard-care (control) group. Follow-up visits are scheduled at 3, 6, 12 and 24 months (Fig. 1). All participants will see their usual-care physicians at each visit to receive usual-care and individualized appropriate treatment according to their background disease, in addition to administration of the study drug.

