#### Measurement of carotid IMT

The protocol and method for measuring carotid IMT have been described in detail previously [25, 31, 32]. In brief, the carotid ultrasound examinations using standardized imaging protocols and systems equipped with >7.5 MHz linear transducers will be performed at each local site and then measured at a core laboratory (Tsukuba University) at baseline and 24 months after randomization. Expert trained sonographers who have attended a lecture on measuring carotid IMT will carry out the procedure according to the Mannheim carotid IMT consensus [33, 34]. The head position and probe angle of the ultrasound approach will be set using a ruler located just cephalad (Fig. 2). Longitudinal B-mode images, perpendicular to the ultrasound beam, with a 3–4 cm imaging depth, will be recorded in the distal common carotid arteries (CCA), carotid bulbs, and proximal internal carotid arteries (ICA) on both sides. The lateral probe incidence is used to obtain CCA images, using external landmarks and an original semicircular protractor developed for this purpose. The mean CCA-IMT indicates the average IMT value of the right and left CCA-IMT, 10 mm from the bulb. The following far wall IMTs will be measured; maximum IMT of the CCA and mean and maximum IMTs of the bulb and ICA. The optimized R-wave gated still frames of the carotid IMT will be stored as JPEG files, with all the parameters collected and measured at the core laboratory. An expert analyzer blinded to the allocation and clinical information of the subjects will measure all the IMT values using an automatic IMT measurement software program (Vascular Research Tools 5, Medical Imaging Applications, Iowa, USA) [35]. The software program identifies the lumen/intima and the media/adventitia borders in this region and calculates the distance between them.

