### Study endpoints

Intima-media thickness (IMT) in the carotid artery is well-established as a surrogate marker for risk of CV diseases and is also useful for evaluating the effectiveness of various types of therapeutic interventions in patients with or without T2DM [35–37]. The primary endpoint in the study is the change in mean IMT of the CCA from baseline to 24 months. The secondary endpoints are the values and changes in parameters after 24 months of treatment, including: (1) mean IMT of the bulb and ICA, (2) max IMT of the CCA, bulb, and ICA, (3) the overall mean of mean IMT of the CCA, bulb, and ICA, (4) the mean of max IMT of the CCA, bulb, and ICA, (5) specific biomarkers including hsCRP, MDA-LDL, NT-proBNP, and high-molecular weight adiponectin, (6) the cardiovascular functional tests listed in Additional file 3 (optional), (7) abdominal circumference and amount of visceral and subcutaneous fat measured by abdominal computed tomography (optional), (8) creatinine-corrected urinary albumin excretion. In addition, the values and changes after 12 and 24 months in several clinical parameters including BP, BW, and BMI and laboratory data (details listed in Additional file 2) will be evaluated. Safety endpoints also include AEs and adverse drug reactions observed during the study.

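### The MMRM named as the missing-data sensitivity analysis cannot show the effect of missing 24-month IMT scans, because IMT has only one post-baseline measurement

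*Protocol article*

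**What the plan says.** All references are to the Protocol article.

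- **Endpoint (Study endpoints):** "The primary endpoint in the study is the change in mean IMT of the CCA from baseline to 24 months".
- **Scan times (Measurement of carotid IMT):** images are taken at the sites and "then measured at a core laboratory (Tsukuba University) at baseline and 24 months after randomization".
- **Visits (Study outline and follow up):** "Follow-up visits are scheduled at 3, 6, 12 and 24 months". No IMT scan is attached to the 3-, 6- or 12-month visits.
- **Primary analysis (Statistical analysis plan):** baseline-adjusted means, "estimated by analysis of covariance of the change in average carotid IMT at 24 months", leaving out patients with a missing value. "The results will be adjusted by allocation factors".
- **Missing data (same section):** the primary analysis is paired "with the mixed effects model for repeated measures (MMRM) being used as a sensitivity analysis to examine the effect of missing data". A further sentence describes an MMRM sensitivity analysis with "outcomes at baseline and 24 months modelled as a function of time, treatment, and treatment-by-time interaction". Secondary endpoints are to be analysed in the same way as the primary one. No other missing-data analysis is named.
- **Withdrawal (Safety, Table 2):** the criteria include adverse effects of the study drug, HbA1c of 12% or more on repeat measurement, and poor adherence.

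**The concern.** An MMRM adds information about missing outcomes when patients who miss the final visit have earlier post-baseline values of the same outcome. For IMT there are none. The plan therefore fixes both a method and a purpose, and the method cannot serve the purpose.

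The risk is one of interpretation. If the two results agree, a reader will conclude that missing scans did not matter, although both analyses would share the same error. If they differ, the reader may blame missing data when the cause is chance baseline imbalance. Table 2 makes loss related to arm and to prognosis plausible: only one arm can withdraw for side effects of ipragliflozin, and poor glycaemic control is itself a withdrawal criterion. The trial is also open-label.

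**Working it through.** **1. The plan's own figures.** From Sample size estimation: difference 0.016 mm, SD 0.06 mm, two-sided 5%, power 80%.

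n per arm = 2 × (1.960 + 0.842)² × 0.06² / 0.016² = 2 × 7.849 × 14.06 = 220.8, so 221 by the normal formula and 222 with the t distribution. The stated 222 is reproduced. Inflating for 5% dropout gives 222 / 0.95 = 233.7, so 234. The planned 240 allows 1 − 222/240 = 7.5% loss. This point changes none of these figures.

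**2. Why the two analyses coincide.** Write y0 and y1 for baseline and 24-month IMT and g for arm. The joint likelihood splits into f(y0 | g) × f(y1 | y0, g).

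- The second factor is y1 = α + βy0 + τg + error. Only patients with a 24-month scan contribute to it, so its estimates b and τ̂ are those of the complete-case ANCOVA. Modelling the change y1 − y0 instead of y1 leaves τ̂ unchanged.
- The first factor uses every patient with a baseline scan and gives the baseline difference between arms, D.
- The MMRM difference at 24 months is τ̂ + bD. The treatment-by-time effect subtracts D:

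  MMRM effect = τ̂ − (1 − b) × D.

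This holds for a common unstructured covariance and the same covariates in both models. If the baseline means are constrained to be equal, the MMRM effect is τ̂ itself. If the MMRM instead models change with baseline as a covariate, each patient has one outcome and the model is the complete-case ANCOVA.

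**3. Numerical check.** Trials with 240 per arm were simulated and the MMRM was fitted by REML and by ML. Assumed inputs: baseline SD 0.10 or 0.15 mm, and nominal dropout of 5% to 15%, either random, baseline-dependent or outcome-dependent. Allocation factors were left out of both models. The largest departure from the identity was below 3e-10 mm. With equal baseline means, the MMRM differed from the ANCOVA by less than 6e-10 mm.

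**4. Size of the baseline term.** If the SD is the same at both times, b = 1 − 0.06² / (2 × SD²), and D has standard deviation SD × √(2/240).

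| Baseline SD (assumed) | b | SD of D | SD of (1 − b) × D |
|---|---|---|---|
| 0.10 mm | 0.82 | 0.0091 mm | 0.0016 mm |
| 0.15 mm | 0.92 | 0.0137 mm | 0.0011 mm |

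The simulations gave 0.0010 to 0.0017 mm, with no systematic dependence on the amount or mechanism of dropout.

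**5. What both analyses miss.** Suppose a fraction p of one arm has no 24-month scan and would have progressed d mm more than that arm's completers. The full-data arm mean then exceeds the completers' mean by p × d, and complete-case ANCOVA misses this amount. The documents give neither p by arm nor d, so these are assumptions.

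| p in one arm | d = 0.01 mm | d = 0.02 mm | d = 0.03 mm |
|---|---|---|---|
| 5% | 0.0005 | 0.0010 | 0.0015 |
| 7.5% | 0.00075 | 0.0015 | 0.00225 |
| 10% | 0.0010 | 0.0020 | 0.0030 |

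For d = 0.02 mm, 0.0010 / 0.016 = 6.25% and 0.0020 / 0.016 = 12.5% of the planned difference. A simulation of the 10% case (2,000 replicates) averaged −0.0161 mm for ANCOVA, −0.0161 mm for MMRM and −0.0142 mm for full data. The MMRM recovered none of the gap.

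**6. A deliberately severe mechanism.** Dropout was made to rise with progression in the ipragliflozin arm and to fall with it in the control arm, with a true effect of −0.016 mm and baseline SD 0.10 mm. At about 5% missing, ANCOVA averaged −0.0206 and MMRM −0.0205; at about 13% missing, both averaged −0.0282. There were 60 trials per scenario, so the Monte Carlo error of each mean is about 0.0054 / √60 = 0.0007 mm. The documents do not support this mechanism as likely. It shows only that the two analyses are displaced together.

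**The case against.** The best defence is that the article is brief, says a statistical analysis plan will follow before database lock, and does not call the MMRM the only sensitivity analysis. The covariates and covariance of the first MMRM are not stated, and the exact identity depends on them. A patient with a 24-month scan but no baseline scan would enter the MMRM only. Planned dropout is just 5%.

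Most of this limits the point without removing it. Leaving out the allocation factors, or using a compound-symmetry or arm-specific covariance, would separate the two estimates slightly. Those are modelling differences, and they do not test departures from missing at random. Patients with only the later scan should be rare, because the baseline scan is scheduled. Leaving detail to a later plan is normal, but here the article itself states the method and its purpose, and the two do not fit.

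Four stronger inferences are not supported:

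- **That informative dropout is the main threat to the primary result.** At the planned 5% dropout, the illustration gives about 0.001 mm. Larger values need assumptions the documents do not supply.
- **That allowing different baseline means biases the MMRM.** Randomisation excludes a systematic difference but not a chance one. The freedom costs a little precision and causes no bias.
- **That MMRM is useless throughout the trial.** HbA1c, blood pressure, weight and BMI are also measured at 12 months, and an MMRM can use those values.
- **That the trial will have no other missing-data analysis.** The article names none, but the later plan is not shown.

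**Conclusion.** The point holds for IMT and for other endpoints measured only at baseline and 24 months. The named sensitivity analysis rests on the same assumption as the primary analysis and uses the same 24-month information. Agreement between them says nothing about missing scans, and disagreement reflects baseline imbalance or model choices. That chance term (SD about 0.001 to 0.002 mm under the assumed baseline SDs) is as large as the illustrated missing-data error of 0.001 to 0.002 mm, so a difference is as easy to misread as agreement.

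The algebra needs no assumption beyond matched covariates and an unstructured covariance. The illustrated error assumes 5% to 10% withdrawal in one arm, 0.02 mm worse progression in those patients, and no 24-month scan for them. Its direction depends on which arm loses them: loss from the ipragliflozin arm flatters the drug, and loss from the control arm does the opposite.

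This should be fixed. It concerns a supporting analysis and leaves the primary analysis, endpoint and sample size as they are.

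**What to change.** For endpoints measured only at baseline and 24 months:

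1. Stop describing the MMRM as the analysis that examines missing data. It may stay as a supplementary model if labelled as such.
2. Add at least one analysis that departs from missing at random, followed by the same ANCOVA. Suitable choices are delta-adjusted multiple imputation taken to a tipping point, or control-based multiple imputation for the ipragliflozin arm. Prespecify and justify the delta range. The documents give only the planned 0.016 mm difference, the expected changes by arm and the 0.06 mm SD as anchors, so the range is the trial team's decision.
3. Optionally, add multiple imputation that uses data already collected after baseline, such as treatment status at each visit and the 12-month HbA1c, blood pressure and weight. This relaxes the missing-at-random assumption but does not depart from it. Patients lost before 12 months lack the 12-month values, and the documents do not show that these variables predict 24-month IMT.

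Keep the MMRM for HbA1c, blood pressure, weight and BMI.

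The cost is a little extra programming in SAS 9.4. No new data are needed, and the change can go into the statistical analysis plan before database lock.
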